### Recruitment {15}

Participants will be recruited within the different departments of PsyQ, other mental health institutions within the region, and directly through general practitioners. General practitioners, mental health institutions, and possible participants will be informed about the study through social media, patient associations, and word to mouth communication. Recruitment started in the first half of 2020 and will continue until the sample size is reached, which will likely be around July 2024.

## Assignment of interventions: allocation

### Sequence generation {16a}

Patients will be assigned to either (1) ERP as usual or (2) personalized ERP. Scientific literature shows that the prevalence of OCD is not determined by gender (a ratio of 1:1) [44]. However, there are differences in symptomatology between the genders, with women presenting more contamination obsessions and men reporting more obsessions of a sexual nature [45, 46]. Furthermore, males with OCD have an earlier age of onset and being of male gender is a prognostic factor for a poor treatment outcome [10, 45, 47]. Since gender is a prognostic factor of treatment response, randomization will be stratified according to gender. There is no gender difference in the prevalence of OCD so the randomization ratio will be 1:1. The allocation sequence is generated by the software package Research Manager. Research Manager is an online research platform which provides multiple tools to manage clinical trials (e.g., encrypted data storage, randomization tools) [48].

### Concealment mechanism {16b}

The allocation sequence is generated by the software package Research Manager. After generation of the sequence, it is not possible to open the randomization table. Only the research assistants have authorisation to randomize participants. There is a strict protocol which assures that the randomization outcome stays concealed. Only one research assistant is aware of the outcome while the other performs the measurement blinded.

### Implementation {16c}

The allocation sequence was generated by the principal investigator before start of the study. Two research assistants will assign participants to interventions.

## Assignment of interventions: blinding

### Who will be blinded {17a}

Since we are investigating two active treatment conditions, both participants and therapist will not be blinded to assignment. All outcome assessors and data analysts will be blinded for intervention assignment.

### Procedure for unblinding if needed {17b}

Unblinding is only permissible in the very rare case when it is necessary for the participants’ health (e.g., when the researchers need to be involved in discussing other treatment steps for the participant).

## Data collection and management

### Plans for assessment and collection of outcomes {18a}

In our study, we will administer a combination of structured clinical interviews and self-report questionnaires. Clinical interviews will be administered by trained outcome assessors. Outcomes of the questionnaires will be collected through the software package Research Manager and stored in encrypted form on a secured server. Measurement moments will be at baseline, 5 weeks of treatment, 10 weeks of treatment (midtest), 15 weeks of treatment, 20 weeks of treatment (posttest), 6 weeks follow-up, 3 months follow-up, 6 months follow-up, and 12 months follow-up. Primary and mediation outcomes will be measured at all measurement moments. Secondary outcomes will be measured at baseline, midtest, posttest, and in all follow-up moments. Control variables will be measured at baseline. For more information on outcomes, see {12}.

### Plans to promote participant retention and complete follow-up {18b}

Participants will be approached by telephone to motivate them to fill out the questionnaires and to see if any help is needed. When participants decide to drop out of the intervention protocol, the reason for dropping out will be noted and participants will be asked to continue to fill out all the measurements.

### Data management {19}

All involved researchers have a thorough understanding of the AVG (Dutch) and GDPR (European) privacy regulations, are certified regarding Good Clinical Practice (GCP), and will ensure that the research adheres to these standards. Data generated with the NiceDay application will be stored in encrypted form on a secured server owned by Sense Health. Sense Health conforms to the Dutch NEN 7510 and international ISO 27001 standards for information security management. The NiceDay app used in the study also conforms to these standards, and any data processed or stored during this research will be handled in a GDPR compliant fashion. This includes measures for tracking explicit consent, anonymizing or pseudonymising data, and limiting access only to approved research personnel. A full overview of the collected variables and how they will be managed can be provided on request. Outcomes of the questionnaires will be collected through Research Manager and stored in encrypted form on a secured server.

### Confidentiality {27}

A subject identification code list will be used to link the data to subjects. This code will be secured, and the key to the code will be safeguarded by the investigator and senior researchers. The Health Care Inspection (Inspectie Gezondheidszorg en Jeugd) and the internal science committee of the Parnassia.

Groep can request access to the data to ensure the quality of the study. All data will be stored for the legal retention period of 15 years.

### Plans for collection, laboratory evaluation, and storage of biological specimens for genetic or molecular analysis in this trial/future use {33}

Not applicable, no specimens will be collected.

## Statistical methods

### Statistical methods for primary and secondary outcomes {20a}

#### Primary outcomes

Multilevel mixed modelling analysis will be used to investigate differences in treatment effect, measured through symptom reduction on the Y-BOCS. Multilevel analysis is especially suitable to analyze repeated measurement data because it takes into account the dependencies among observations nested within individuals. Another advantage of this methodology is its ability to handle missing data. We will start with a three-level structure with treatment effect (Y-BOCS score) as dependent variable, repeated measures at the first, individuals at the second, and treatment condition at the third level. We will then add age, gender, Ehealth literacy scale scores, and medication use to the model as covariates. We will determine the covariance structure empirically. Effect sizes and clinical significant change according to the Jacobson and Truax criteria will be calculated to estimate respectively the magnitude of the treatment effect and the significance of the results for clinical practice [49]. All analyses will be done both according to the intention-to-treat principle and per protocol in order to gain as much insight as possible into the efficacy of the intervention, as recommended by CONSORT.

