## Methods: participants, interventions and outcomes

### Study setting {9}

The study will be performed at multiple sites of anxiety disorders departments of PsyQ. PsyQ is part of the Parnassia group, a large urban ambulatory mental health organization in the Netherlands. Other departments in the regions of The Hague and Rotterdam will be made aware of the study and will be asked to refer eligible patients.

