### Eligibility criteria {10}

To be eligible to participate in this study, a participant must meet all the following criteria: (1) an OCD diagnosis according to DSM-5, (2) not having received any treatment for OCD in the past 3 months, (3) stable medication for at least three months, and (4) willing to refrain from following other treatment for OCD and keep medication stable during the experimental part of the study. When entering the naturalistic follow-up phase, these restrictions will be released.

Our exclusion criteria will only relate to our obligation to offer appropriate care and to guarantee patient safety. Only patients who suffer from severe comorbidity which necessitate other treatment (psychosis, addiction/intoxication) will be excluded from participation in this study. Since the treatment and questionnaires will be in Dutch or English insufficient fluency in the Dutch or English language is also a criterion for exclusion.

All therapists providing treatment are fully licensed to give cognitive behavioral therapy and must complete a training in exposure skills specifically designed for this study. Furthermore, therapist providing the experimental therapy must complete a training in working with the smartphone application NiceDay. All therapists will be supervised 2-weekly by an experienced and licensed therapist.

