### Sample size {14}

A statistical power analysis to estimate sample size for longitudinal, correlated data was performed [42, 43]. This analysis revealed that with an alpha of 0.05, an estimated correlation of 0.5 between measurements and a power of 0.85 the sample size needed to detect a small to medium effect (*f* = 0.35) is 160. We expect a small to medium effect since a large effect is unlikely due to the small differences between the conditions. Also, we are not interested in finding a small effect; therefore, we choose to calculate a sample size large enough to detect a clinically relevant effect with a medium effect size. Therefore, we propose a total sample size of 160 patients.

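### The primary model puts treatment condition at the third level and has no therapist term; if therapists are nested in arm, or their effects differ materially by arm, the standard error of the arm contrast is too small

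*Protocol article*

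**What the plan says.** Protocol article, Statistical methods {20a}, Primary outcomes: the Y-BOCS model starts from three levels, namely measurements, patients, and treatment condition at the top. Age, gender, eHealth literacy and medication use are then added as covariates. The stated merit of the method is that "it takes into account the dependencies among observations nested within individuals". Secondary outcomes repeats the three levels and the covariates. Neither model contains a therapist or site term. Under Mediation analysis, by contrast, condition is a fixed two-category factor.

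Intervention description {11a}: both arms receive weekly individual sessions with a therapist. In the experimental arm the therapist also gives weekly feedback, whose content depends partly on the therapist's clinical judgement.

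Eligibility criteria {10}: all therapists are licensed, trained in exposure and supervised every two weeks. In addition, a "therapist providing the experimental therapy must complete a training in working with the smartphone application NiceDay". Study setting {9} adds: "The study will be performed at multiple sites of anxiety disorders departments of PsyQ".

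Sample size {14} rests on "an estimated correlation of 0.5 between measurements" and names no other dependence. The number of therapists, their caseloads, and whether they treat one arm or both are not given.

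**The concern.** Condition is the contrast under test and has two categories. It cannot serve as a random grouping level, and placing it there does not capture variation between therapists. The model therefore treats patients as independent given arm, although each has 20 weeks of treatment from a therapist who treats other trial patients too.

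What follows depends on how therapists relate to arms. If each therapist works in one arm only, differences between therapists become part of the difference between arms. The standard error then omits a real source of variation, and the primary test rejects too often. If each therapist treats both arms, the shared part of the therapist effect cancels from the contrast, and only the part that differs by arm can make the standard error too small.

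**Working it through.** **Inputs from the article.** Two-group comparison, N = 160 (80 per arm), 1:1 allocation, alpha 0.05 (taken as two-sided), power 0.85, effect 0.35, correlation 0.5 between measurements, nine measurement moments for the primary outcome.

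**Inputs assumed.** ICC of 0.02, 0.05 and 0.10 for the analysed outcome; k = 5 to 16 trial patients per therapist.

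**1. The plan's own figure.** Read 0.35 as a standardised mean difference (the article writes it as f) and compare patient means over m = 9 measurements. The variance factor is (1 + 8 × 0.5)/9 = 0.556. Then n per arm = 2 × (1.960 + 1.036)² × 0.556 / 0.35² = 81.4, rounded up to 82, so 164 in total. At 80 per arm the power is 0.844. This is close to 160, but it is a reconstruction: other two-sided readings tried give other totals (for example 176 with five measurements and 294 with a single endpoint). It assumes independent patients and leaves no allowance for therapists. The type I error results below do not depend on it.

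**2. Therapists fully nested in arm.** Design effect DE = 1 + (k − 1) × ICC. True type I error = 2 × [1 − Φ(1.96/√DE)]. Effective N = 160/DE. The correct interval is √DE times the naive one. Power uses step 1: 0.35/√(0.556 × 2/80) = 2.970, so power = Φ(2.970/√DE − 1.96).

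| ICC | k | DE | Type I error | Effective N | Interval wider by | Power |
|---|---|---|---|---|---|---|
| 0.02 | 5 | 1.08 | 5.9% | 148 | 4% | 0.82 |
| 0.05 | 5 | 1.20 | 7.4% | 133 | 10% | 0.77 |
| 0.05 | 10 | 1.45 | 10.4% | 110 | 20% | 0.69 |
| 0.10 | 10 | 1.90 | 15.5% | 84 | 38% | 0.58 |
| 0.10 | 16 | 2.50 | 21.5% | 64 | 58% | 0.47 |

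Power is for a test with the correct standard error and before any small-sample correction, which would lower it further when therapists are few.

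A simulation (20,000 runs per setting) agrees. With 10 therapists per arm (k = 8), the naive test rejects in 6.6%, 9.0% and 13.0% of null trials at ICC 0.02, 0.05 and 0.10; the formula gives 6.6%, 9.2% and 13.3%.

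**3. Every therapist treats both arms equally.** Let c be the patients per therapist in each arm and s the share of therapist variance that differs by arm. The true variance over the naive variance is about 1 − ICC + c × s × ICC, so the naive standard error is too small only when c × s exceeds 1.

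- Common effect only (s = 0): the ratio is 0.98 to 0.90. Simulated type I error is 3.9% to 4.6%. The naive standard error is 1% to 5% too large (1/√0.98 = 1.01; 1/√0.90 = 1.05).
- Half the variance differs by arm (s = 0.5, c = 4): the ratio is 1.02 to 1.10. Simulated type I error is 4.9% to 6.0%.

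**The case against.** A reader might infer that standard errors are too small whenever outcomes cluster by therapist. The documents do not support that. The app training is an extra requirement on top of training common to all therapists, which fits therapists working in both arms as well as in one. Nothing in the article assigns therapists to arms, and with full crossing the naive test is close to nominal or slightly conservative. This objection stands, and the point is conditional because of it.

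The upper end of the range is one corner of the assumptions: ICC 0.10 and 16 patients per therapist, or 160/16 = 10 therapists for the whole trial. The article does not favour that corner; common training and supervision give no reason to expect a high ICC, though they do not remove clustering. This also stands.

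The primary outcome is change from baseline to posttest, and therapists can influence scores only after baseline. That stands too: the ICC that matters is that of the change or baseline-adjusted score.

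A further defence is that random effects belong in an analysis plan that is not shown, and that the article only starts from this structure and settles the covariance empirically. This holds in part. The quoted sentence about dependence within individuals is correct as a general statement. But the article does fix the levels, twice, and gives the third to the contrast under test. Choosing a covariance structure for repeated measures would not add a therapist term.

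**Conclusion.** The point holds in conditional form. The stated hierarchy is misassigned and leaves out the therapist, whichever arrangement applies. The direction and size of the consequence depend on facts that the article does not give.

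Under full nesting, with the assumed ICC and caseloads, the true type I error is about 6% to 21%, and about 10% in the middle case. Partial nesting, or effects that differ materially by arm, moves the error rate in the same direction to a lesser degree. Under full balanced crossing with a common effect it is about 4% to 4.6%, and the loss is a little precision. The article does not establish that the trial's error rate is inflated. It states a model that would not protect against inflation if therapists are nested. This should be corrected before analysis; confidence is medium because the therapist-arm arrangement is unknown.

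**What to change.** 1. In both outcome models, enter condition as a fixed effect with its interaction with time, in line with its fixed role under Mediation analysis.
2. Make therapist the third level, as a random effect, with a small-sample degrees-of-freedom correction. The effect must be able to act on change: a therapist intercept that is constant over time cancels from a baseline-to-posttest difference. Either let it vary with time, or adjust for baseline and apply it to the post-baseline scores.
3. If therapists treat both arms, add a random therapist-by-condition term.
4. State the number of therapists and whether they treat one arm or both, and report the therapist ICC with the results.

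Site as a fixed effect is optional.

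**Cost.** This is a change of wording plus a therapist identifier for each patient. Trial status reports 102 of 160 patients included, so the model can still be amended before analysis; identifiers for patients already treated would have to be confirmed or recovered. Under nesting the cost in precision is not trivial: the interval is about 20% wider at ICC 0.05 with 10 patients per therapist and about 58% wider at the extreme. On the step 1 reconstruction, power at N = 160 falls from 0.84 to about 0.69 and 0.47. That loss is already present in the design; the present model would only hide it. Under balanced crossing the change costs little and may recover some precision.

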### Outcomes {12}

#### Primary outcome measure

##### Yale-Brown Obsessive–Compulsive Scale (Y-BOCS)

Primary outcome is a decrease in symptom severity, measured with the Y-BOCS, between the measurements taken at baseline and at posttest.

The Y-BOCS is a semi-structured clinical interview which assesses the severity of obsessions and compulsions separately and is the gold standard to measure OCD severity in clinical practice and scientific research. The Y-BOCS consists of 10 items which are rated on a 4-point Likert scale. The internal consistency and validity of the Y-BOCS have proven to be good. Moreover, the Y-BOCS is sensitive to change. The Y – BOCS has been validated in a Dutch clinical population [30]. The Y-BOCS will be administered at each assessment moment by telephone by trained outcome assessors.

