#### Secondary outcomes

Multilevel mixed model analysis will be used to assess differences in quality of life, anxiety states, and depressive symptoms between the conditions. We will start with a three-level structure, with respectively quality of life, anxiety states, and depressive symptoms as dependent variable, repeated measures at the first, individuals at the second, and treatment condition at the third level. Age, gender, Ehealth literacy scale scores, and medication use will be added as covariates.

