#### Mediation analysis

In order to assess differences between the groups in self-efficacy and experiential avoidance, we will apply multilevel analysis with the scores on the SEQ-OCD and AAQ-II scores at baseline, midtest, and posttest will serve as dependent variables, treatment condition (ERP as usual versus personalized ERP) as a fixed (dichotomous) factor. Furthermore, we will use the macro of Preacher and Hayes and apply bootstrapping methods to assess the possible mediating effect of changes in self-efficacy and experiential avoidance on subsequent treatment effects.

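### The primary and secondary outcome models name treatment condition as a third hierarchical level, although the two randomised arms are a fixed contrast and are coded that way in the mediation models

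*Protocol article*

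**What the plan says.** Under Statistical methods {20a}, Primary outcomes, the Y-BOCS model starts as a three-level structure with "repeated measures at the first, individuals at the second, and treatment condition at the third level". The next step reads "We will then add age, gender, Ehealth literacy scale scores, and medication use to the model as covariates". The Secondary outcomes section repeats the structure ("individuals at the second, and treatment condition at the third level") for quality of life, anxiety states and depressive symptoms, followed by "Age, gender, Ehealth literacy scale scores, and medication use will be added as covariates". Neither section describes condition in any other way.

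The Mediation analysis section handles the same variable differently. For the SEQ-OCD and AAQ-II it enters "treatment condition (ERP as usual versus personalized ERP) as a fixed (dichotomous) factor".

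Two other places bear on this. Sequence generation {16a} fixes the number of conditions at two: "Patients will be assigned to either (1) ERP as usual or (2) personalized ERP". Outcomes {12} defines the primary outcome as a decrease in severity "measured with the Y-BOCS, between the measurements taken at baseline and at posttest".

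**The concern.** A level in a multilevel model is a set of exchangeable units, treated as drawn from a wider population and given a random effect. Occasions within patients fit that description. The two arms do not: they are the only two treatments of interest, and the trial exists to estimate the difference between them.

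Placing condition at the top level turns that difference into a variance estimated from two units. An analyst who follows the sentence gets no coefficient for personalized ERP against ERP as usual, and none for how the arms differ in change over time. An analyst who departs from it has to choose the treatment term and the tested contrast without support from the published text. Both concern the primary analysis. The mediation section shows that the correct coding was available, so the article is also inconsistent from one model to the next.

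**Working it through.** **Inputs.** Two conditions and a 1:1 ratio (Sequence generation {16a}). Total 160, so 80 per arm; alpha 0.05 (two-sided assumed), power 0.85, correlation 0.5, effect 0.35 (Sample size {14}). Nine measurement occasions, with the Y-BOCS at each (Plans for assessment {18a}).

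**1. The plan's own figure.** Read 0.35 as a standardized mean difference on the average of nine occasions (an assumption; the article labels it *f*).
- Variance factor: (1 + (9 − 1) × 0.5)/9 = 5/9 = 0.556.
- Total N = 2 × 2 × ((1.960 + 1.036)/0.35)² × 0.556 = 162.9, or 164 after rounding up per arm. This is within 3% of 160.
- Power at 80 per arm is 0.844, against the stated 0.85.

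**2. Degrees of freedom of the literal model.**
- Between-condition variance: 2 units − 1 = 1 df.
- With a fixed condition term added and the level kept: 2 units − 2 fixed parameters (intercept and condition) = 0 df. The fixed term and the random effect cannot be separated.

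**3. What a variance on 1 df can tell.**
- The 2.5% and 97.5% points of chi-square on 1 df are 0.00098 and 5.02. A 95% interval therefore runs from 1/5.02 ≈ 0.20 to about 1018 times the estimate.
- With equal arms, the REML estimate is zero whenever the between-arm mean square falls below the within-arm one, that is, when the ordinary |z| is below 1. With no effect, P(|Z| < 1) = 0.683. In 20,000 simulated trials the share was 0.678.
- With an effect, the share depends on how 0.35 is read, so it is a range. On a single score, z = 0.35/√(2/80) = 2.21, giving about 11%. On the nine-occasion average, z = 0.35/√(2 × 0.556/80) = 2.97, giving about 2.4% (simulated 2.5%). If 0.35 is Cohen's f, d = 0.70 and even a single score gives z ≈ 4.4 and about 0.03%.
- For d = 0.35 the implied component is 0.35²/2 = 0.061. With nine occasions and correlation 0.5, the middle 95% of simulated estimates ran from 0.000 to 0.161.

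**4. The two codings on one simulated data set** (160 patients, nine occasions, correlation 0.5, true time-averaged difference 0.35).

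| Coding | What the fit reports |
|---|---|
| Condition as a level, no fixed term | Overall intercept; arm variance 0.004 (SE 0.020); no arm difference, CI or p-value |
| Condition as a fixed factor | Arm difference 0.142 (SE 0.111), p = 0.20 |

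Both fits address the time-averaged difference, so only the coding differs. The point is what each model reports, not that this data set reached significance.

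**5. After the correction.** With condition fixed and patients as the top level there are 160 − 2 = 158 between-patient df. Under the assumptions of step 1, simulated type I error is 0.051 and power 0.837. These figures are for the time-averaged difference.

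**The case against.** The best reply is that the hierarchy is loosely worded and a fixed comparison is meant. The Primary outcomes section says that the model serves to compare treatment effects and promises effect sizes; the Secondary outcomes section speaks of differences between the conditions; and the mediation section shows that the authors know how to code the variable. Neither outcome section calls condition random or mentions an arm variance. This stands as evidence of intent. It does not repair the text, because no sentence in either section ties the comparison or the effect sizes to a model term.

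A second reply is that the structure is only a starting point, and that a full list of model terms commonly belongs in an analysis plan that is not shown. This also stands: the lack of listed interaction terms would not be a finding alone. The finding is the explicit statement that condition is a level, made twice. The listed next step adds four covariates and does not withdraw it.

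A third reply is that the mediation section concerns other dependent variables, so the clash is between models rather than within one. That is fair, but the variable and the design are the same, and the sections should agree.

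A reader might infer that the treatment effect will never be estimated or tested, or that the trial cannot answer its first objective. The documents do not support that. It describes the literal model, not the declared aim, and even the literal model yields shrunken predictions for the two arms and a variance component that can be tested, however poorly. Randomisation and data collection are untouched.

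**Conclusion.** The specification is wrong as written in both outcome sections and conflicts with the mediation section. Read literally, the primary model holds condition only as a two-unit grouping level on 1 df. Its variance is estimated as zero in about 68% of trials under no effect, and no parameter expresses the between-arm difference in change that defines the primary outcome. The 1 df, the 0 df and the 68% follow from having two arms of equal size and do not depend on the assumed effect. The figures under an effect do, and the conclusion does not rest on them.

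A fixed comparison is probably intended, so this is an error in the published model to be corrected, not proof that the planned comparison will be absent. Nothing in the correction calls for a different sample size. The power of 0.837 rests on reading 0.35 as a standardized difference averaged over nine occasions; whether that reading suits the baseline-to-posttest contrast is a separate question.

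**What to change.** In both Primary outcomes and Secondary outcomes under {20a}:
- Remove treatment condition from the list of levels, leaving measurements nested in patients.
- Enter condition, time and condition-by-time as fixed effects, with the listed covariates kept. The coding then agrees with the mediation section.
- State that the treatment effect is the model-based between-arm contrast in change from baseline to posttest, with its 95% CI and p-value, and that effect sizes derive from it.

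Do not keep the third level alongside a fixed condition term. The cost is one sentence in each of two sections, with no extra patients, visits or data.

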### Relevant concomitant care permitted or prohibited during the trial {11d}

During the active treatment phase of 20 weeks, participants are asked to refrain from any other form of care. After concluding the active treatment phase, a treatment-free period of 6 weeks is followed by a booster session. After the booster session, patients will enter a naturalistic follow-up period in which they are allowed to seek help the way they would normally do when confronted with an increase of anxious symptoms (e.g., visiting one’s general practitioner or seeking sources of symptom relief, e.g., using pharmacotherapy).

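### The declared primary outcome is the Y-BOCS change from T0 to T4, but the primary model names no treatment-by-time contrast at T4 and leaves baseline Y-BOCS out of its covariates

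*Protocol article*

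**What the plan says.** Visit labels here follow the article's Abstract: T0 baseline, T1 to T4 at weeks 5 to 20, T5 to T8 follow-up.

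- **Outcome** (Outcomes {12}): "Primary outcome is a decrease in symptom severity, measured with the Y-BOCS, between the measurements taken at baseline and at posttest".
- **Aim of the model** (Statistical methods {20a}, Primary outcomes): "Multilevel mixed modelling analysis will be used to investigate differences in treatment effect, measured through symptom reduction on the Y-BOCS".
- **Structure** (same section): the Y-BOCS score is the dependent variable, with "repeated measures at the first, individuals at the second, and treatment condition at the third level".
- **Covariates** (same section): "We will then add age, gender, Ehealth literacy scale scores, and medication use to the model as covariates".
- **Visits** (section {18a}): "Primary and mediation outcomes will be measured at all measurement moments". That makes nine Y-BOCS assessments, four of them after T4.
- **Follow-up** (section {11d}): "After the booster session, patients will enter a naturalistic follow-up period in which they are allowed to seek help the way they would normally do".
- **Mediator models, for comparison** (Mediation analysis): "scores on the SEQ-OCD and AAQ-II scores at baseline, midtest, and posttest will serve as dependent variables", with condition entered as a fixed two-category factor.

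**The concern.** The outcome section points to one between-arm quantity, the difference in change from T0 to T4. The primary analysis section is detailed about levels, covariates, covariance structure and clinical-significance criteria, yet nothing in it picks out that quantity. It gives no time term, no interaction, no T4 contrast and no set of visits. Treatment appears only as a grouping level. With two units, such a level cannot support a variance estimate and does not replace a treatment effect. The mediator section names its visits and enters treatment as a fixed factor, so the primary model is specified less sharply than a secondary one.

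Two things are at stake. First, several different tests fit the text, and the choice could be made after the data are seen. Second, the explicit covariate list omits the Y-BOCS score already collected at baseline, which under one reading costs precision that is available for nothing.

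**Working it through.** **Inputs.** Sample size {14}: alpha 0.05 (two-sided assumed, since the article does not say), correlation rho = 0.5, power 0.85, effect 0.35 labelled f, N = 160. Sequence generation {16a}: 1:1 allocation, so 80 per arm. Variances are in units of sigma², the Y-BOCS variance at one visit, with equal correlation between visits.

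**1. The plan's own figure.** For a difference averaged over m visits the variance factor is v = (1 + (m − 1)rho)/m, and n per arm = 2(1.960 + 1.036)² v/d².

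- m = 9, with 0.35 read as a standardised mean difference d: v = (1 + 8 × 0.5)/9 = 0.556 and total N = 164. Power at 80 per arm is 0.844. This is close to the stated 160 and 0.85.
- T4 change score, d = 0.35: v = 1.00, N = 294.
- T4 adjusted for baseline, d = 0.35: v = 0.75, N = 220.
- 0.35 taken literally as f (d = 2f = 0.70 for two groups): the two-sided averaged or single-visit calculations give N of 42 to 74, and noncentral-F repeated-measures tests give 10 to 58.

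Of the two-sided variants tried, only the nine-visit average with 0.35 as d comes near 160. A one-sided average over three visits gives 158, so the match is suggestive but not unique.

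**2. Reading (i): a treatment main effect over all nine visits.** T0 is included, where no treatment effect is expected. As a share of the T4 effect (the time courses are assumptions):

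- constant from T1: 8/9 = 0.89;
- linear to T4, then held: (0 + 0.25 + 0.5 + 0.75 + 1 + 1 + 1 + 1 + 1)/9 = 6.5/9 = 0.72.

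With d = 0.35 at T4 and 80 per arm, power is 0.75 and 0.57 respectively, against 0.84 with no dilution.

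**3. Reading (ii): an unconstrained T4-minus-T0 contrast.** The change-score variance is 2(1 − rho). Conditioning on baseline gives 1 − rho².

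| rho | Change score | Baseline-conditioned | Saving |
|---|---|---|---|
| 0.3 | 1.40 | 0.91 | 35% |
| 0.5 | 1.00 | 0.75 | 25% |
| 0.7 | 0.60 | 0.51 | 15% |

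A generalised least squares check at rho = 0.5, with five and with nine visits, gave 1.00 for the unconstrained contrast and 0.75 when the arms share one T0 mean. The 25% saving is worth as much as N = 160/0.75 = 213.

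**4. Power at T4.** Power = Φ(d√(80/2)/√v − 1.96).

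- d = 0.35: v = 1.00 gives Φ(2.214 − 1.96) = 0.60; v = 0.75 gives Φ(2.556 − 1.96) = 0.72.
- d = 0.70: 0.993 and 0.999.

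**The case against.** The strongest reply is that the article does not describe a nine-visit average. The nine occasions come from the data-collection section, the outcome section limits the primary outcome to T0 and T4, and the analysis section itself speaks of symptom reduction. Visit sets and contrasts may also be spelled out in a full protocol or analysis plan that is not shown. This stands against four stronger conclusions that a reader might draw:

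- **That the plan's effect is diluted by design.** Dilution follows from reading (i) only. That the sample size fits such an average makes the reading plausible, but does not show that it is intended.
- **That the plan suffers both dilution and a wider interval.** The two belong to different models. Under reading (i) the variance at rho = 0.5 is 0.556 sigma², below the 0.75 of the baseline-adjusted T4 contrast.
- **That omitting baseline from the covariate list by itself loses 25%.** If T0 is one of the repeated responses and the arms share a T0 mean, the variance is already 0.75. The loss arises with an unconstrained contrast or, at rho = 0.5, with an unadjusted T4 score.
- **That the test departs from the registered outcome.** No registry record is at hand; the comparison is with the outcome declared in the article.

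The reply does not remove the mismatch. The article chose to state a model structure and a covariate list, and what it states does not yield the quantity it declares.

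**Conclusion.** The mismatch holds: the declared outcome is the T0-to-T4 change, and the stated primary model fixes no term that estimates it, gives treatment only as a two-unit level, and omits baseline Y-BOCS. The size is conditional. Under reading (i) the tested effect is about 89% or 72% of the T4 effect, given the assumed time courses. Under reading (ii) baseline conditioning saves 25% of the variance at the plan's rho, and 35% to 15% for rho from 0.3 to 0.7, assuming equal variance at T0 and T4. The rise in power from about 0.60 to 0.72 requires 0.35 to be d; as f, power is already about 99% and the gain is in precision only. This is worth correcting because it leaves the confirmatory test open, but it does not show that the trial will give a wrong answer.

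**What to change.** In Statistical methods {20a}, Primary outcomes:

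1. Enter treatment as a fixed factor, with time as a categorical factor and treatment by time, and drop treatment as a level.
2. Name the between-arm contrast at T4 as the primary test.
3. Model the post-baseline visits with baseline Y-BOCS, and baseline by time, as covariates. Do not use T0 as both response and covariate.

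The alternative of keeping T0 in the response with equal arm means is less attractive here. The Limitations section says that participants are not blinded to allocation at the baseline measures, so that equality should not be written in as a constraint. Neither form repairs a T0 score that knowledge of the allocation has shifted.

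Restricting the fit to the treatment phase is optional once the T4 contrast is named, because with categorical time and the interaction the later visits do not dilute it. Gender, the stratification factor, is already in the model.

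The cost is analysis wording only. No new data are needed, and with 102 of 160 participants included at the time of the article, the text can be settled before analysis.
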